#### Details of statistical analyses

##### Primary analysis: diagnosis and Gleason scoring

We will quantify the concordance of the AI system’s cancer diagnosis (positive/negative), GS and ISUP grade with the reference standards in the tuning, internal validation and external validation cohorts using the metrics described below. The analysis will be conducted on slide level (AQ, AUH, KUH-1, KUH-2, MUL, RUMC, SFR, STHLM3, SUH, UKK, WNS), anatomical location level (MLP, SFI, SCH) and/or patient level (KUH-1, SCH, SFI, SFR, SPROB20) depending on the granularity of the available reference standards.

##### Cancer diagnosis

Sensitivity (true positive rate) and specificity (true negative rate) will be used to quantify the agreement of negative/positive diagnosis for prostate cancer with the reference standard. CIs for sensitivity and specificity will be computed using the non-parametric bootstrap over cases. We will additionally report the area under the receiver operating characteristics curve (AUROC) and confusion matrices.

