External validation cohorts are fully external relative to the development set (no overlap with respect to patients, laboratory or scanner) or partly external (no overlap with respect to patients or laboratory, but digitisation performed using a scanner that is also present in the development set). Fully external validation set cohorts include Aichi Medical University (AMU), Aarhus University Hospital (AUH), KUH morphological subtypes (KUH-2), Mehiläinen Länsi-Pohja (MLP), Medical University of Lodz (MUL), Synlab Switzerland (SCH), Synlab Finland (SFI), Synlab France (SFR), Spear Prostate Biopsy 2020 (SPROB20), University Hospital Cologne (UKK), Hospital Wiener Neustadt (WNS). Partly external validation set cohorts include: Aquesta Uropathology morphological subtypes (AQ), partially scanned on a scanner present in the development set and partially scanned on an external scanner. The external nature of the validation set cohorts fulfils Requirements 4–6.

All data splits were performed on patient level, that is, all slides and resulting WSIs from a given patient were allocated to the same data partition in order to avoid information leakage between development and validation sets. If a patient was biopsied on several occasions, all biopsies were included and allocated together. Any samples lacking patient identifiers were assigned to development data to avoid the risk of slides from any patients ending up in both development and evaluation cohorts.

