##### ISUP grade

Quadratically weighted Cohen’s kappa (QWK) will be used to quantify the agreement of the ISUP grade with the reference standard. In addition, we will also report linearly weighted Cohen’s kappa (LWK) and confusion matrices. To allow calculating weighted kappas, ISUP grades will be treated as ordinal variables (0–5), with benign encoded as 0. CIs will be computed using the non-parametric bootstrap over cases.

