### Secondary analysis: PNI detection

We will quantify the concordance of the AI system’s prediction of the presence of PNI with the reference standards in those internal and external validation cohorts where a reference standard is available (MUL, SCH, STHLM3 and SUH). The tuning set has an insufficient number of PNI samples for evaluation and will be included in the training. The concordance will be quantified using unweighted Cohen’s kappa. In addition, we will also report AUROC, sensitivity (true positive rate), specificity (true negative rate) and confusion matrices. Slides reported as borderline for PNI will be considered negative. The analysis will be conducted on slide level. CIs will be computed using the non-parametric bootstrap over cases.

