#### Subgroup analysis D

We will measure the performance of the AI system in terms of the primary objective on subgroups of slides representing morphological subtypes of benign and malignant tissue that are usually hard for pathologists to diagnose. We evaluate the performance of the AI system in the STHLM3 morphological subtypes internal validation cohort, the KUH-2 external validation cohort and the AQ external and partly external validation cohorts. See table 4 for the distribution of morphological subtypes reported in each cohort. We will evaluate performance in terms of cancer diagnosis and, additionally, Gleason scoring, where applicable to the subtype.

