#### Sensitivity analysis B

To put the discrepancies between the AI system and the reference standards in the context of interobserver variation between pathologists, we will quantify all-against-all pairwise agreements in panels consisting of pathologists and the AI system.

For the primary objective, the analysis will be conducted on subsets of the STHLM3 (ImageBase) and RUMC (PANDA Radboud) internal validation cohorts and on the full UKK and WNS external validation cohorts, which were assessed by a panel of pathologists and have per-pathologist grades available in addition to their consensus (see table 2). For the secondary objectives of cribriform cancer and PNI detection, the analysis will be conducted on subsets of the STHLM3 internal validation cohort, assessed by panels of pathologists (see table 3).

We will calculate the average pairwise agreement (QWK and LWK for the primary objective, unweighted Cohen’s kappa for the secondary objectives) for all the pathologists in the panels, including the AI system, and compare the average AI-pathologist agreement to the average pathologist-pathologist agreement. CIs will be computed using bootstrapping, as detailed in a previous study.^47^

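### The bootstrap for confidence intervals leaves its resampling unit undefined, most naturally slides rather than patients, and gives a zero-width interval whenever sensitivity or specificity is observed at 100%

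*Protocol article*

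**What the plan says.** Under Cancer diagnosis the protocol article says "CIs for sensitivity and specificity will be computed using the non-parametric bootstrap over cases". The sections on Gleason score, ISUP grade, cancer extent, cribriform cancer and PNI each use one sentence, "CIs will be computed using the non-parametric bootstrap over cases". Only Sensitivity analysis B differs: "CIs will be computed using bootstrapping, as detailed in a previous study".

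The level of scoring varies. For the primary analysis, "The analysis will be conducted on slide level (AQ, AUH, KUH-1, KUH-2, MUL, RUMC, SFR, STHLM3, SUH, UKK, WNS"). MLP, SFI and SCH are analysed by anatomical location, and some cohorts by patient: "patient level (KUH-1, SCH, SFI, SFR, SPROB20) depending on the granularity of the available reference standards". Cribriform cancer and PNI are scored by slide only; for PNI, "Slides reported as borderline for PNI will be considered negative. The analysis will be conducted on slide level".

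Predefined data partitions makes the patient the unit for splitting the data and adds: "If a patient was biopsied on several occasions, all biopsies were included and allocated together". Repeat scans of one slide are reduced to a single image for validation, but nothing comparable is said about several slides from one patient.

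Subgroup analysis D covers "subgroups of slides representing morphological subtypes of benign and malignant tissue", with the counts in Table 4. The Power section makes point estimates and their confidence intervals the central objective and gives this as a reason for having no sample-size calculation.

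**The concern.** Two separate problems arise.

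The first is the resampling unit. Slides from one man share his disease and tissue handling, so the AI's errors on them may well be correlated. The plan respects this grouping when it splits the data but does not mention it for the intervals. If slides or locations are resampled individually, the bootstrap treats correlated results as independent and understates the standard error.

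The second is the boundary. A bootstrap can only redraw what was observed. If every slide in a group is called correctly, every resample is all correct and the interval has no width. This holds for patient resampling too.

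Both matter because the study tests no hypothesis and leans on its intervals to convey uncertainty. Intervals that are too short would overstate how well generalisation has been established, and a zero-width interval on a handful of slides of a rare subtype would read as certainty.

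**Working it through.** The article gives no interval width or target precision, so there is no stated figure to reproduce. It also gives no confidence level, no full-cohort number of slides per patient and no intra-patient correlation. I assume 95% and show ranges for the other two.

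**What is a case?** Usage in the article is mixed.
- Slide-like: the overview of analyses lists an IHC comparison by cases, and Subgroup analysis E describes the same comparison by slides. Sensitivity analysis D speaks of cases in which a slide is predicted benign. Sensitivity analysis E refers to borderline cases among slides first classed as false positives.
- Patient-like: Subgroup analysis C speaks of individuals with prior cancer treatment and then of too few cases. Representative sampling refers to consecutive clinical cases.

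In the analysis sections the slide-like sense predominates, so for a slide-level metric slides are the natural reading. It is not the only possible one.

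**Clustering, if slides are resampled.** With m slides per patient and intra-patient correlation ρ:
- design effect DE = 1 + (m − 1)ρ
- interval length relative to the correct length = 1/√DE
- actual coverage = 2Φ(1.96/√DE) − 1

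With m = 8 (assumed):

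| ρ | DE | Interval too short by | Coverage |
|---|---|---|---|
| 0.05 | 1.35 | 14% | 0.908 |
| 0.10 | 1.70 | 23% | 0.867 |
| 0.20 | 2.40 | 35% | 0.794 |

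The only slide-to-patient ratio in the article is 119/81 = 1.47, from a selected SUH subset, so it is not a full-cohort cluster size. At m = 1.47, coverage is 0.947 at ρ = 0.05 and still 0.922 at ρ = 0.50. At m = 5, coverage is 0.926 at ρ = 0.05 and 0.856 at ρ = 0.20.

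A beta-binomial simulation supports the formula. It used 196 patients with 10 slides each (an assumed layout, close to the 1959 MUL slides), a true proportion of 0.95, 1000 data sets and 500 resamples:

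| ρ | Coverage, slide bootstrap | Coverage, patient bootstrap | Width ratio, patient/slide |
|---|---|---|---|
| 0 | 0.964 | 0.962 | 1.00 |
| 0.1 | 0.868 | 0.949 | 1.37 |
| 0.2 | 0.773 | 0.945 | 1.66 |
| 0.3 | 0.710 | 0.946 | 1.90 |

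With only 81 patients and 2 slides each at ρ = 0.2, coverage was 0.885 by slide and 0.901 by patient. In small cohorts, patient resampling alone does not restore 95%.

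**Boundary, any unit.** If n of n are correct, every resample gives 100%, so the interval is [100%, 100%]. Treating slides as independent:
- Clopper-Pearson lower limit = 0.025^(1/n)
- chance of an all-correct sample when true sensitivity is 95% = 0.95^n

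| Group | n | Chance all correct | Exact lower limit |
|---|---|---|---|
| PIN-like cancer, STHLM3 | 3 | 0.86 | 29.2% |
| Small cell cancer, KUH-2 | 4 | 0.81 | 39.8% |
| Pseudohyperplastic cancer, STHLM3 | 9 | 0.63 | 66.4% |
| Pseudohyperplastic cancer, KUH-2 | 24 | 0.29 | 85.8% |
| UKK or WNS, if all slides counted | 50 | 0.08 | 92.9% |
| MUL, if all slides counted | 1959 | about 0 | 99.8% |

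The last two rows use whole-cohort slide counts to show scale; the denominators for sensitivity and specificity are smaller. Exact enumeration of the percentile bootstrap at true sensitivity 95% gives coverage of 0.707 at n = 24 and 0.484 at n = 13 (foamy gland cancer, KUH-2). Non-zero cells of Table 4 hold 1 to 38 slides.

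**The case against.** The strongest reply is that the article never says slides are resampled or that clustering is ignored. A reader might infer that the plan knowingly treats slides as independent, so that its intervals are certain to be too narrow. The text does not support that. The unit is undefined, a patient reading is possible, and the result also needs positive correlation within patients. This part stands, and the point is therefore conditional.

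Second, the size rests on assumed cluster sizes and correlations. That also stands: the one ratio shown implies little loss, though it comes from a subsample. Eight slides per patient suits specificity better than sensitivity, which depends on the number of positive slides per patient. In addition, a scanner or reader that is constant throughout a cohort adds nothing to within-patient correlation in that cohort.

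Third, Subgroup analysis D names no interval method, and the confusion matrices promised for the main diagnosis analysis would let a reader compute exact limits. The first half is fair, so the subgroup consequence holds only if the same bootstrap is carried over. The second half does not repair a printed [100%, 100%].

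Fourth, details of the bootstrap could sit in an analysis plan or appendix that is not shown. That may settle the unit. It does not remove the boundary problem, which follows from the method the article itself names.

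It would also be too broad to call this the only interval method, because Sensitivity analysis B cites a bootstrap from an earlier study whose details are not shown. Zero width at 100% does not carry over to RMSE in general.

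**Conclusion.** The point holds in conditional form. The stated method leaves its unit open in a plan with three levels of scoring, and the most natural reading gives intervals that are too narrow for slide- and location-level metrics if errors correlate within patients. Under 8 slides per patient and ρ of 0.05 to 0.20, coverage is about 91% to 79%. It is close to nominal when patients contribute few slides. Patient-level results (SPROB20 and the patient-level parts of KUH-1, SCH, SFI and SFR) are not affected, and point estimates do not change.

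The zero-width interval at 100% needs no assumption about the unit. It is a practical problem in groups of a few to a few dozen slides, if the bootstrap is used there, and negligible in the large cohorts.

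**What to change.** Replace the phrase about cases by an explicit rule: for every slide- or location-level metric, patients are drawn with replacement and all their slides or locations are kept together. For sensitivity and specificity observed at 0% or 100%, and in small subgroups such as those of Table 4, report Wilson or Clopper-Pearson limits, using an effective sample size (n divided by the design effect) where slides are clustered within patients.

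This takes a sentence or two in the plan and a small change in code. Patient grouping should be available for the validation data, because the splits were made by patient and samples without identifiers went to development. The locked model is untouched. The price is somewhat wider intervals: in the simulated layout, 1.37 to 1.90 times as wide at ρ of 0.1 to 0.3, and no wider at ρ = 0.

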##### Gleason score

Quadratically weighted Cohen’s kappa (QWK) will be used to quantify the agreement of Gleason scoring with the reference standard. In addition, we will also report linearly weighted Cohen’s kappa (LWK) and confusion matrices. To allow calculating weighted kappas, Gleason patterns (eg, 3+4) will be encoded into ordinal variables following earlier studies^43^,^45^ as follows: benign (0), 3+3 (1), 3+4 (2), 4+3 (3), 3+5 (4), 4+4 (5), 5+3 (6), 4+5 (7), 5+4 (8), 5+5 (9). CIs will be computed using the non-parametric bootstrap over cases.

##### ISUP grade

Quadratically weighted Cohen’s kappa (QWK) will be used to quantify the agreement of the ISUP grade with the reference standard. In addition, we will also report linearly weighted Cohen’s kappa (LWK) and confusion matrices. To allow calculating weighted kappas, ISUP grades will be treated as ordinal variables (0–5), with benign encoded as 0. CIs will be computed using the non-parametric bootstrap over cases.

### Secondary analysis: cancer extent prediction

We will quantify the concordance of the AI system’s prediction of linear cancer extent expressed in millimetres with the reference standards in those tuning, internal validation and external validation cohorts where a reference standard is available (AUH, KUH-1, STHLM3, SUH, STG, MLP, SCH, SFI, SFR). The concordance will be quantified using root mean squared error (RMSE). In addition, we will also report Pearson’s linear correlation coefficient and show scatter plots of predicted millimetre cancer length versus millimetre cancer length reported by the reference standard. The analysis will be conducted on slide level (AUH, KUH-1, STHLM3, SUH, STG, SFR), anatomical location level (MLP, SFI, SCH) and/or patient level (MLP, SCH, SFI, SFR) depending on the granularity of the available reference standards (see online supplemental appendix 2). CIs will be computed using the non-parametric bootstrap over cases.

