### Study design

The aim of this study is to develop the AI system described above and validate its diagnostic performance on retrospectively collected cohorts. To carry out the study, historical data, including medical records, pathology reports and digitised images, have been collected for cases where both the AI system and human pathologists make diagnostic assessments. The study design involves two independent phases: AI system development and AI system validation as shown in figure 1. The development phase involves an iterative cycle of refining the model design and hyperparameters using predefined development and tuning cohorts for model training and estimation of the effects of design choices on diagnostic performance. Once the overall performance on the development and tuning sets is deemed to have reached a plateau and further changes to the model design no longer yield meaningful improvements, a design freeze will take place and the final AI model will be graduated to the validation phase. This design achieves complete isolation between the model development and the retrospective validation to avoid any information leakage, which could lead to overly optimistic validation results. All model parameters and hyperparameters, including selection of any classifier thresholds, will be set based on the development and tuning cohorts, and no adjustments or tweaking will be conducted on the validation cohorts, which will remain entirely untouched during the development phase. Development data, on the other hand, can be freely accessed without risk of bias at any point, allowing optimisation of the AI model design prior to the validation phase of the study.

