#### Predefined data partitions

The process of splitting the data cohorts into development, tuning, and internal and external validation sets was conducted adhering to the requirements for data partitions and is described below (see figure 1 for an overview). The characteristics of the data cohorts included in this study are described in detail in online supplemental appendix 2.

The development set was sampled from the following cohorts: Capio S:t Göran Hospital (STG), Radboud University Medical Center (RUMC), Stavanger University Hospital (SUH) and Stockholm3 (STHLM3). From the RUMC, STHLM3 and SUH cohorts, the patients who were not allocated to tuning or validation sets (see below) were assigned to the development set (approximately 80% of patients). Given the limited size and skewed grade distribution of the STG cohort, it was fully allocated into the development set. The development set covers several clinical laboratories and scanner devices as well as a large degree of variation in tissue morphology and the clinical characteristics of patients, in part due to the largest cohort, STHLM3, originating from a population-based screening trial (Requirements 1–2). Each of the development cohorts was further split into 10 cross-validation folds by randomly allocating patients to folds, stratified by the maximum slide level ISUP grade of each patient.

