The tuning set was sampled from the following cohorts: Karolinska University Hospital (KUH-1), RUMC and STHLM3. The entire KUH-1 cohort was assigned to tuning and represents a fully external cohort relative to the development set (ie, different patients, laboratory and scanner). This set also corresponds to the European external validation cohort of the PANDA challenge.^17^ The subsets of the RUMC and STHLM3 cohorts assigned to the tuning set represent internal data relative to the development set (ie, different patients but the same laboratories and scanners) and correspond to the PANDA public test sets in Kaggle (ie, the PANDA tuning sets). The tuning sets allow for evaluating the effects of model design changes on data that is independent of the development set, direct comparison with state-of-the-art models from PANDA, and in the case of KUH-1, assessing the generalisation performance of the model prior to design freeze (ie, performance on data coming from different patients, laboratories and scanners compared with the development data) (Requirement 3). A subset of slides belonging to the PANDA Swedish tuning set was allocated to the internal validation set for reasons related to patient stratification and the inclusion of specific subsets of interest in the internal validation (see below).

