The internal validation set was sampled from the following cohorts: RUMC, STHLM3 and SUH, consisting of patients who were not part of the development or tuning sets but whose biopsies were obtained from the same clinical laboratories and scanned with the same scanners as the development and tuning set samples. The STHLM3 internal validation set includes the following subsets, supplemented with randomly sampled patients to achieve a total 20% fraction of patients assigned to tuning and validation: ImageBase,^36^ Swedish private test set in Kaggle (ie, PANDA Swedish internal validation set),^17^ PNI multiobserver validation set^41^ and rare morphological subtypes set.^42^ Including these samples as subsets of the internal validation set will facilitate (internal) comparisons with results obtained in the papers referenced in the preceding sentence. The SUH internal validation set includes the following subsets, supplemented with randomly sampled patients to achieve a 20% fraction of patients assigned to validation: all patients (n=25) with multiple recuts of their biopsy tissue blocks, and patients (n=81) corresponding to a random selection of 119 slides stratified on ISUP grade (to be rescanned repeatedly over time for an AI temporal stability study). The STHLM3 subsets allocated into the internal validation set were selected based on being particularly valuable for the evaluation phase of the study, while the SUH subsets will be used as validation sets in upcoming follow-up studies involving the AI model developed here, hence cannot be assigned to the development set. The RUMC internal validation set includes the RUMC private test set in Kaggle (ie, PANDA RUMC internal validation set),^17^ supplemented with randomly sampled patients to achieve a total 20% fraction of patients assigned to tuning and validation.

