### Sensitivity analyses

#### Sensitivity analysis A

We will evaluate the reproducibility of the AI system’s output in terms of the primary and secondary objectives on WSIs obtained from the same slides on multiple scanners. The analysis will be conducted on the STHLM3 tuning and internal validation cohorts and the MUL external validation cohort, which contain WSIs rescanned on different scanners (see table 1). In the STHLM3 cohort, a subset of slides (n=287) have been rescanned on five scanners: Aperio AT2 DX, Grundium Ocus40, Hamamatsu NanoZoomer 2.0-HT C9600-12, Hamamatsu NanoZoomer XR C12000-02 and Philips IntelliSite UFS. In the MUL cohort, a subset of slides (n=503) have been rescanned on two scanners: Grundium Ocus40 and Philips IntelliSite UFS. We will quantify the reproducibility of the AI predictions across scanners using QWK, and LWK and the percentage of slides with discordant predictions for each objective and each pair of scanners. We will additionally report confusion matrices.

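### The cancer-extent analysis lists STG among tuning and validation cohorts, although STG lies wholly in the development set

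*Protocol article*

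**What the plan says.** In the protocol article, the section Secondary analysis: cancer extent prediction restricts the evaluation to tuning, internal validation and "external validation cohorts where a reference standard is available (AUH, KUH-1, STHLM3, SUH, STG, MLP, SCH, SFI, SFR"). It then sets the unit of analysis and names STG a second time: "The analysis will be conducted on slide level (AUH, KUH-1, STHLM3, SUH, STG, SFR"). The measures are root mean squared error and Pearson's correlation, with bootstrap intervals.

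The section Predefined data partitions assigns STG differently: "Given the limited size and skewed grade distribution of the STG cohort, it was fully allocated into the development set". For the other sets it says "The tuning set was sampled from the following cohorts: Karolinska University Hospital (KUH-1), RUMC and STHLM3", and "The internal validation set was sampled from the following cohorts: RUMC, STHLM3 and SUH". The fully and partly external cohorts are then listed by name, and STG is not one of them.

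**The concern.** The extent section describes its list as cohorts with tuning or validation data, and one entry has none. For a locked model, a result on slides from its own development set measures fit, not performance on unseen cases. The article gives overly optimistic validation results as its reason for separating the two phases.

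A reader of the results would see an STG row next to cohorts such as AUH or MLP, with nothing to show that it is a different kind of figure. An analyst following the section literally would produce that row.

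**Working it through.** No power or sample-size figure bears on this point. The check is set membership: each cohort in the extent list is compared with its allocation in Predefined data partitions.

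| Cohort in the extent list | Allocation | Has tuning or validation slides? |
|---|---|---|
| KUH-1 | tuning, entire cohort | yes |
| STHLM3 | development, tuning, internal validation | yes |
| SUH | development, internal validation | yes |
| AUH, MLP, SCH, SFI, SFR | fully external validation | yes (5 cohorts) |
| STG | development, entire cohort | no |

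Count: 1 + 1 + 1 + 5 = 8 of the 9 listed cohorts have tuning or validation slides. The remaining one, 9 − 8 = 1, is STG.

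Three other parts of the article show which of the two statements is likely to be the slip.

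- The primary analysis omits STG from its slide-level list, although Table 2 gives STG a slide-level grading reference for 247 slides.
- The cribriform and perineural invasion lists also omit STG.
- The partition section says that STG, STHLM3 and MUL slides were scanned on several instruments and that only one image per slide enters the validation sets. It gives selection rules for STHLM3 and MUL only. Table 1 shows 74 + 67 + 247 = 388 STG images for the 247 slides in Table 2. Scoring STG would therefore need a choice among scans that the article does not make.

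All three fit STG being a development-only cohort. The allocation appears to be the intended statement and the two entries in the extent section the error.

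With STG removed, the extent list has 8 cohorts (AUH, KUH-1, STHLM3, SUH, MLP, SCH, SFI, SFR), each with tuning or validation slides. The slide-level list becomes AUH, KUH-1, STHLM3, SUH and SFR.

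**The case against.** The best defence is that the lists give source cohorts and the partition decides which slides count. STHLM3 and SUH are also named, although approximately 80% of patients in those cohorts are development data, and nobody would read that as a plan to score training slides. On the same reading STG contributes nothing and its name is a stray entry. That is a likely account of how it got there. It does not remove the contradiction, because a cohort with no eligible slides does not belong in the list, and the section names it twice.

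The shared heading in Tables 1 to 3, which groups development, tuning and internal validation cohorts, does not help: it is a group label and gives STG no validation share. Out-of-fold cross-validation predictions may have been meant, but the section does not say so, and these would still be development results.

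Two stronger readings are tempting, and the documents do not support them.

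- A reader might infer that the separation of phases is broken, given the statement "This design achieves complete isolation between the model development and the retrospective validation". That rule stops validation data from influencing the model, and the same section allows free access to development data. Scoring STG leaks nothing from any validation cohort. The fault is one of labelling.
- A reader might also fault Sensitivity analysis A, which measures cross-scanner agreement "using QWK, and LWK and the percentage of slides with discordant predictions for each objective and each pair of scanners", on the ground that kappa is undefined for a millimetre output. It is not. Quadratic weighting needs only a disagreement weight. With (x − y)² on raw values, weighted kappa equals 2·s_xy / [s_x² + s_y² + (mean_x − mean_y)²], which is Lin's concordance coefficient with 1/n variances. Linear weighting works likewise with |x − y|. So reproducibility of the extent output would have a usable result. What remains is that no tolerance is stated for calling two millimetre predictions discordant, which is missing detail rather than an error.

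**Conclusion.** The contradiction stands, and nothing in the article resolves it. Its reach is narrow: one cohort of nine, in one secondary objective. The 247 slides are an upper figure, because they come from the grading reference table.

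Calling the STG figures in-sample assumes that the locked extent model was fitted on the whole development set, as the partition implies. If the extent model had left STG out of fitting, STG would still be a development cohort and not a validation one.

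The article describes no pooling of extent results across cohorts, so the other eight cohorts' figures do not change. The generalisation claim rests on the external cohorts, which are untouched. By how much the STG figures would flatter the model cannot be said from the documents.

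**What to change.** In Secondary analysis: cancer extent prediction, delete STG from the cohort list and from the slide-level list. If an STG figure is wanted, report it apart from the validation results, use out-of-fold cross-validation predictions, label it development performance, and state which scan is used for slides imaged more than once.

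The cost is two small wording changes and one fewer cohort result for one secondary objective. No new data are needed. Optionally, add to Sensitivity analysis A the difference in millimetres above which two predictions count as discordant.
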